## Abstract

**Background:**

Burnout and poor well-being are serious problems in the workforce all over the world. Especially in academia, high pressure is evident. Therefore, addressing burnout is essential for enhancing academic staff well-being. Acceptance and commitment therapy (ACT), which aims to enhance psychological flexibility skills comprising present moment awareness, value-based actions, and differentiation of thoughts from self, has been found to be a promising approach to enhance workers well-being and work satisfaction.

**Objective:**

The purpose of this study was to first develop and describe our acceptance and commitment therapy–based WELLS course, aimed at supporting academic staff well-being and working life skills, offered to academic staff. The second aim was to report the mixed methods study design protocol to explore the participants’ experiences of the effects of the course.

**Methods:**

We will conduct a single-arm, nonrandomized, and mixed methods study with baseline, postintervention, and 6-month follow-up assessments. We will use an explanatory sequential design in which qualitative data are used to explain and deepen the quantitative findings. The quantitative part of the study aims to recruit 300 participants from the University of Helsinki. Questionnaire data will be collected from the participants 3 times: at the beginning, at the end, and 6 months after the course for well-being–related measures such as burnout and working life skills such as time management and psychological flexibility. The participants will be clustered based on their initial burnout risk score using latent profile analysis. Differences in participants’ dropout, participation forms, and changes in well-being and working life skills during the course will be analyzed with mixed ANOVA. Qualitative data will be collected from reflective journals written at the end of the course, participants’ written goal statements, and interviews among willing participants. Reflective journals will be analyzed with qualitative content analysis, and interviews will be analyzed using thematic analysis.

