Job-related or occupational burnout can be conceptualized as an aspect of eudaimonic well-being and is a critical problem all around the world in occupational contexts [11]. Job-related burnout comprises 3 dimensions: exhaustion, cynicism related to one’s job, and reduced professional efficacy [12]. One way to conceptualize job-related burnout is the job demands–resources model, which indicates that burnout is a product of an imbalance between job demands and resources [13]. As mentioned earlier, academic staff can experience high demands in their work, such as an increasing number of students, a decline in perceived job control, administrative problems, unfair rewards, and supervision of programs [1,3,4]. Thus, the model highlights the importance of personal resources in maintaining the balance between resources and demands [13].

On the other hand, psychological flexibility, understood as opening up to difficult thoughts and emotions and moving toward important values, can act as a central personal resource [14]. Psychological flexibility describes the ability to recognize and accept difficult thoughts and emotions (instead of avoidance) mindfully and engage in value-based actions [14,15]. Psychological flexibility is the key concept in acceptance and commitment therapy (ACT), which is a form of third-wave therapy and aims to develop psychological flexibility [15]. ACT is grounded in functional contextualism, which seeks to understand psychological events (such as thoughts, emotions, and behaviors) by examining their function within a specific context rather than isolating them as individual entities [16]. This approach emphasizes the relationship between an event and its context to determine its purpose or role, assuming that behavior is not inherently good or bad; its value depends on the context in which it occurs [17]. Additionally, relational frame theory underpins this approach by focusing on how we understand and use language and thoughts through learned relationships between concepts [18]. Relational frame theory views cognition and language as processes of relational learning, where the meaning of an event or thought is shaped by its relationship to other events or thoughts [18].

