### Measures and Data Collection

#### Quantitative Data

First, for RQs 1 to 3, validated self-assessment questionnaire data will be collected before (T1), after (T2), and 6 months after the course (T3). The questionnaires measure emotional, psychological, and social well-being (Mental Health Continuum-Short Form) [39]; psychological flexibility (Work-related Acceptance and Action Questionnaire) [40]; perceived stress (Perceived Stress Scale) [41]; and risk of burnout (15-item Bergen Burnout Indicator) [42]. Psychometric properties will be further evaluated in the present sample via internal consistency (Cronbach α) and factor structure (confirmatory factor analysis). A 6-month follow-up is used to examine how potential changes during the course persist or change over time. Psychological flexibility especially is understood as a process that develops gradually through ongoing practice and integration into daily life, and changes may therefore continue to evolve beyond the course period [21]. Furthermore, this timeframe is also consistent with prior research in the field, which commonly uses follow-up periods of 6 months [43-45].

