### Analyses

#### Statistical Analyses

For RQ 2, the effects of the course are analyzed with repeated-measures ANOVA and hierarchical modeling to see the changes at the group level. In addition, for RQ 1, the participants will be clustered based on their initial burnout risk score to compare the effects of the course in different risk groups using latent profile analysis and repeated-measures ANOVA. For RQ 3, attrition analyses are conducted using chi-square tests of independence and odds ratios to examine whether dropout rates differ across latent burnout profiles and between group-based and self-guided participation formats.

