### Strengths and Limitations

This study’s key strength lies in its versatile mixed methods approach. First, by using latent profile analysis to profile participants’ baseline burnout scores (RQ 1), we explore burnout as a complex and heterogeneous construct and move beyond aggregated group-level averages to a more person-oriented perspective, which has gained more popularity in the last decades [52]. We aim to additionally explore participants’ self-reported changes during the course quantitatively (RQ 2) but also deepen and contextualize these findings with qualitative insights (RQ 4). This integration allows us to identify not only whether change occurs but also to explore how and why participants perceive change happens or does not happen, and whether qualitative experiences converge with or diverge from quantitative trends. Thus, the study may provide a more nuanced understanding of what participants experience during the course and which aspects may be most useful for them. Finally, we also aim to examine whether burnout profiles and the format of participation may influence engagement in the course (RQ 3), which may provide practical information regarding how and to whom the course may be most beneficial.

Furthermore, the study design also benefits from its flexibility, as well as its ease of execution and implementation in university work environments. As the study takes place in an online environment with no facilitation, a flexible schedule, and is continuously open, the study does not require excessive resources and is relatively easy to carry out. Additionally, the flexible design may mitigate some of the burden on participants, as they are able to complete the course at their own pace, thus also following ethical research principles.

However, the study design also possesses limitations. The flexible schedule design also indicates that a control group cannot be used, and thus we are not able to randomize participants, which precludes, for instance, a randomized controlled trial. A nonrandomized design may also introduce selection bias, which may limit the generalizability of the results. Therefore, the conclusions regarding the effectiveness of the course are limited.

A potential limitation of the mixed methods design is that qualitative data are collected from a subsample, which may not fully represent the broader quantitative sample, potentially limiting the integration of the findings and the generalizability of the results.

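### Latent profiles appear to rest on one burnout score and are then analysed as known groups, which gives severity bands, dilutes dropout contrasts and inflates contrasts in burnout change

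*Protocol article*

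**What the plan says.** The Abstract (Methods) has participants "clustered based on their initial burnout risk score using latent profile analysis". Statistical Analyses says that "the participants will be clustered based on their initial burnout risk score to compare the effects of the course in different risk groups", and names the tools for this comparison: "using latent profile analysis and repeated-measures ANOVA". For dropout (RQ 3) it names chi-square tests and odds ratios across profiles.

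Other sections point to a richer construct. Background states: "Job-related burnout comprises 3 dimensions". Quantitative Data names the instrument for "risk of burnout (15-item Bergen Burnout Indicator") and plans a confirmatory factor analysis of the questionnaires. Strengths and Limitations defends the method in these words: "we explore burnout as a complex and heterogeneous construct and move beyond aggregated group-level averages". That section and Results both speak of burnout scores in the plural.

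Results already reports three profiles at T1, with 265 enrolled and 113 completers. Setting and Participants will stratify interview sampling by the same profiles.

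**The concern.** There are two linked problems.

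- **Indicators.** A mixture model on one score can separate people only by where they lie on that score. It cannot tell someone who is mainly exhausted from someone who is mainly cynical if their scores are equal. The argument for a person-oriented method is then largely lost, and the profiles become a cut-up severity scale.
- **Use of the profiles.** Chi-square tests, odds ratios and ANOVA, as ordinarily run, put each person in one group and take that group as correct. For an outcome outside the burnout scale, such as dropout, misassignment mixes the groups and pulls them together. For change in burnout, the T1 value both forms the group and enters the change, so regression to the mean pushes the groups apart.

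At stake are the dropout comparison in RQ 3, the claim in RQ 1 and RQ 2 that the course works differently by profile, and the profile strata for the RQ 4 interviews.

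**Working it through.** The article gives no separation, entropy, class shares or T1-T2 correlation, so there is no figure of its own to reproduce. Every input not taken from the article is an assumption.

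**1. One score gives bands.** With one indicator and equal class variances, the most likely class changes only at cut-points on that score, so the classes are ordered intervals. More than one class is also weak evidence of real types. In 100 simulated samples of 265 from one continuous distribution without classes, BIC chose:

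- one class in 99 normal samples;
- two classes in 94 samples at skewness 0.8;
- two classes in 99 samples at skewness 1.15.

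Three classes arose at most once in 100, so skew alone does not readily explain the three profiles in Results.

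**2. Dropout.** Assumed class shares are 40/40/20% and true dropout is 48/58/70%. Overall that is 0.4×0.48 + 0.4×0.58 + 0.2×0.70 = 56.4%. For comparison, 152/265 = 57.4% had not completed at the data cut, some of whom may still be in progress. The true top-minus-bottom difference is 22 points.

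Dropout in an assigned group is the sum over true classes of (share of that class in the group × its dropout). Take adjacent classes 2 SD apart on one score:

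- The assigned top group is 80.6% high, 19.3% middle and 0.1% low: 0.806×0.70 + 0.193×0.58 + 0.001×0.48 = 67.7%.
- The assigned bottom group is 84.1% low, 15.9% middle and 0.1% high, which gives 49.6% before rounding of the shares.
- The visible difference is 18.1 points, a shrinkage of 18%.

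Numerical integration at other separations, with chi-square power at N=300:

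| Separation on the score used | Misassigned | Visible difference | Shrinkage | Power (0.72 with true classes) |
|---|---|---|---|---|
| 1.5 SD | 30% | 16.2 points | 26% | 0.42 |
| 2.0 SD | 21% | 18.1 points | 18% | 0.52 |
| 2.5 SD | 14% | 19.4 points | 12% | 0.59 |
| 2.6 SD (√3×1.5) | 13% | 19.6 points | 11% | 0.61 |
| 4.3 SD (√3×2.5) | 2% | 21.6 points | 2% | 0.71 |

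The last two rows are three conditionally independent scores, each separated by 1.5 or 2.5 SD. If all three shift in parallel, their total has separation √3 times that of one score and classifies exactly as well as the three together. Simulated versions put the upper end a point or two higher (up to 28%), so the range should be read as rounded.

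**3. Change in burnout.** Assume equal variances at T1 and T2, correlation r, a mean change of −0.3 SD, and no profile effect beyond this. Then the expected change given T1 is −0.3 − (1−r)×T1, with T1 in SD units. Cutting T1 at 40% and 80% gives group means of −0.97, 0.27 and 1.40 SD.

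- r = 0.5: changes of 0.18, −0.43 and −1.00; gap 0.5×(1.40+0.97) = 1.18 SD.
- r = 0.8: changes of −0.11, −0.35 and −0.58; gap 0.2×2.37 = 0.47 SD.

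In 1,000 simulated samples of 113 completers, the test of change by group rejected in 99.7% (r = 0.5) and 80% (r = 0.8).

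**The case against.** **The single score is a reading.** No sentence says total score. The plurals in Results and in Strengths and Limitations could mean several scores per person, or one score for each of many people. That stands: the single-score reading is likely, because both places that specify the clustering use the singular, but it is not certain. Either way the indicators need naming.

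**Severity groups may be what is wanted.** Statistical Analyses calls them risk groups, and Principal Findings expects heterogeneous levels. Strengths and Limitations does not itself mention exhaustion, cynicism or efficacy. So a reader should not infer that RQ 1 cannot be answered at all. Bands are an answer, though a thin one for the rationale given.

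**More indicators need not classify better.** This also stands. With parallel profiles the total loses nothing, so the table is no argument for three scores over their total. The argument for dimension scores is that only they can reveal non-parallel patterns.

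**Slices and misclassification are partly alternatives.** If the profiles merely cut a continuum, there is no true class to miss, and the loss is that of categorising a continuous score. The shrinkage applies only if classes are real.

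**A condensed article may omit the assignment rule.** True: its absence alone is no fault, BCH can be run as a weighted ANOVA, and hierarchical modelling is also named for RQ 2. But the article does name its tests for profiles, and in ordinary use they take membership as known.

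**Conclusion.** The point holds in a limited form. As worded, the profiles rest on one burnout score and can only be severity bands, which sits badly with the three-dimensional construct and the person-oriented rationale.

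The named tests then mislead in two directions. Dropout differences between real classes shrink by about 2% to 26% at assumed separations of 1.5 to 2.5 SD per indicator, and little if classes are well separated. Differences in burnout change are inflated, by 0.47 to 1.18 SD between top and bottom groups at assumed correlations of 0.8 to 0.5. Outcomes correlated with burnout, such as stress, would be affected in part.

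A reader might infer that profile differences are biased toward zero throughout. The documents do not support that: it applies to dropout and similar external outcomes if classes exist, and the direction reverses for burnout itself.

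**What to change.** In the Abstract (Methods) and Statistical Analyses:

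- Name the T1 dimension scores of the 15-item indicator as the profile indicators, provided the planned confirmatory factor analysis supports them.
- Relate profiles to dropout and other external outcomes by a bias-corrected three-step method (BCH weights or maximum likelihood), and report entropy and class sizes.
- Add an analysis with T1 burnout kept continuous, which also covers the case where the profiles only cut a continuum.
- State that profile differences in burnout change will not be read as differential effects without allowing for regression to the mean. Three-step weights correct classification error and do not by themselves remove this.

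The items are already collected, so no new data are needed. The cost is slightly wider intervals and a little more analysis work. It is best settled before the first data cut is published and before interviewees are drawn by profile in fall 2026.

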**Results:**

As of March 2026, a total of 265 participants had enrolled in the course and given their consent to participate in the research. The current data are being analyzed, and the results are expected to be published in late 2026 or early 2027.

**Conclusions:**

If the intervention proves successful, it may serve as an important tool for improving academics’ well-being, working life skills, and engagement by understanding how this intervention can help academic staff members with different initial burnout levels. In addition, it can help to understand and solve individual challenges related to well-being in the academic workplace.

## Introduction

### Background

The work-related well-being of academics has been shown to be generally poor and has deteriorated over time [1]. Studies have reported, for example, that people working in education are at higher risk of work-related stress than those in other occupations [1,2]. There are several aspects influencing the well-being of academic staff, and they have experienced increased demands on their work because of, for example, an increasing number of students, technology-based learning, and diversity in the student population [3]. In addition, a decline in perceived job control has also been observed [1]. A recent review study by Shen and Slater [4] showed that the causes of academic staff stress are related, for example, to feelings of heavy workload, administrative problems, unfair rewarding, and program supervision. In addition, high expectations and a competitive atmosphere, including publication targets, were perceived as causing stress [4]. It is clear that academic staff are in need of services to support their well-being.

Well-being is a multilayered concept that is usually very difficult to define [5]. While a much-used concept, positive mental health is often used similarly with the term “mental well-being,” although they need to be considered separately [6]. The dual continual model of well-being considers not only the positive aspects of well-being but also the absence of negative symptoms in well-being [7]. The dual continual model of well-being divides well-being into hedonic and eudaimonic well-being, emphasizing both the absence of mental health problems and the presence of well-being [7]. The hedonic perspective on well-being emphasizes the subjective experience of positive emotions, such as pleasure and happiness, and the absence of negative emotions, as the eudaimonic perspective on well-being emphasizes the psychological functioning and living a meaningful life [8]. Mental well-being incorporates hedonic aspects, such as experiencing positive emotions (ie, feeling good), and eudaimonic aspects related to optimal functioning (ie, functioning well) in one’s life [8-10].

Job-related or occupational burnout can be conceptualized as an aspect of eudaimonic well-being and is a critical problem all around the world in occupational contexts [11]. Job-related burnout comprises 3 dimensions: exhaustion, cynicism related to one’s job, and reduced professional efficacy [12]. One way to conceptualize job-related burnout is the job demands–resources model, which indicates that burnout is a product of an imbalance between job demands and resources [13]. As mentioned earlier, academic staff can experience high demands in their work, such as an increasing number of students, a decline in perceived job control, administrative problems, unfair rewards, and supervision of programs [1,3,4]. Thus, the model highlights the importance of personal resources in maintaining the balance between resources and demands [13].

On the other hand, psychological flexibility, understood as opening up to difficult thoughts and emotions and moving toward important values, can act as a central personal resource [14]. Psychological flexibility describes the ability to recognize and accept difficult thoughts and emotions (instead of avoidance) mindfully and engage in value-based actions [14,15]. Psychological flexibility is the key concept in acceptance and commitment therapy (ACT), which is a form of third-wave therapy and aims to develop psychological flexibility [15]. ACT is grounded in functional contextualism, which seeks to understand psychological events (such as thoughts, emotions, and behaviors) by examining their function within a specific context rather than isolating them as individual entities [16]. This approach emphasizes the relationship between an event and its context to determine its purpose or role, assuming that behavior is not inherently good or bad; its value depends on the context in which it occurs [17]. Additionally, relational frame theory underpins this approach by focusing on how we understand and use language and thoughts through learned relationships between concepts [18]. Relational frame theory views cognition and language as processes of relational learning, where the meaning of an event or thought is shaped by its relationship to other events or thoughts [18].

Psychological flexibility is based on six basic processes: acceptance, cognitive defusion, being present, self-as-context, values, and committed actions [19]. *Acceptance* means willingly embracing thoughts and emotions as they occur without trying to change or avoid them, and *cognitive defusion* can be defined as seeing thoughts and emotions as mental events instead of truths [15]. *Being present* means engaging with the present moment instead of worrying about the past or the future, and *self-as-context* can be defined through viewing oneself as an observer of thoughts instead of letting them define oneself [19]. *Values* are meaningful aspects of our lives which can be identified and clarified, and *committed actions* mean taking purposeful actions in line with the values instead of going through life without thinking about what is important [14,15,19]. By helping individuals clarify their values and take purposeful actions, ACT fosters a sense of purpose and direction, which is associated with greater life satisfaction and well-being [15].

Over 40 years of research have demonstrated that psychological flexibility is associated with a range of positive outcomes, including improved mental health, enhanced emotional well-being, and greater life satisfaction [19]. It has been linked to reduced symptoms of depression, burnout, and anxiety, increased quality of life, and better coping strategies in the face of workplace stress [20-22]. The application of ACT in workplace settings has gained considerable attention, as organizations increasingly recognize the importance of employee well-being for both productivity and job satisfaction [23]. Studies have shown that ACT interventions can effectively reduce workplace stress, improve mental health outcomes, and enhance overall well-being [20,24]. For instance, Flaxman and Bond [25] conducted a randomized controlled trial examining the impact of an ACT-based stress management program on public sector employees. The results revealed significant reductions in stress and anxiety, as well as improvements in job performance and psychological flexibility [25]. Participants reported greater acceptance of challenging work-related thoughts and feelings, which facilitated more adaptive coping strategies [25]. Similarly, a meta-analysis by A-Tjak et al [26] highlighted the efficacy of ACT in occupational settings, demonstrating moderate-to-large effect sizes for improvements in psychological flexibility and reductions in work-related stress and burnout. The analysis underscored the potential of ACT to foster a supportive work environment that prioritizes employee well-being [26]. Although derived from nonacademic work contexts, these findings suggest that ACT may also be a valuable intervention for academic workers.

Despite the positive effects of ACT-based interventions on workers’ well-being, there has been a lack of such interventions targeted at academic staff, especially in online intervention formats [21,27]. Online interventions allow individuals to engage in more flexible support through materials that are constantly available, which may help to address barriers to seeking help, a key challenge for many who could benefit from such interventions [28]. Moreover, online interventions may be particularly valuable in workplaces with a large or geographically dispersed workforces, also including those with remote or hybrid work models (such as universities), as online programs also require fewer physical resources [29]. Thus, online interventions may provide substantial potential to be more scalable, accessible, and cost-effective than in-person interventions [28-30].

Although used more rarely, online ACT-based interventions have already shown promise in effectively improving mental well-being in a variety of contexts [28], including occupational contexts [29]. Despite this, far fewer online ACT-based interventions have been offered to workers [21], and to our knowledge, no current publications explore online ACT-based interventions for university staff specifically, regardless of their potential.

Although increasingly accessible, a common issue among online intervention research is participant engagement [21]. Engagement in this context refers to how users interact with an online intervention, namely through participants’ adherence to the intervention, particularly within the context of a study [31]. Specifically, this indicates initial uptake via enrollment and early interaction with intervention features, and the extent to which participants continue to use the intervention as intended over time. Low engagement and dropping out of the intervention before the intended end of the intervention often disrupt the ability of online programs to deliver effective treatment and complicate research conclusions [27,28].

Despite this, factors such as baseline symptoms of, for instance, burnout and whether the online intervention is completely self-guided (indicating no live interaction with others) or partially guided (indicating a form of live interaction during the intervention through a facilitator or peer interaction) have been found to potentially support engagement in online interventions [21,27]. Thus, exploring individual differences in participants’ experiences, such as baseline burnout, and the format of delivery may help clarify what types of online interventions work, and for whom, in terms of adherence and dropout within a study context.

In addition to psychological flexibility, effective time management is crucial for academics to balance their multifaceted responsibilities and maintain well-being, and thus should be considered when designing interventions for academic staff. Time management involves setting goals, prioritizing tasks, and allocating time efficiently [32]. A recent meta-analysis [33] showed that time management was moderately related to job performance, academic achievement, and well-being, and that time management also showed a negative relationship with distress. According to this study, time management enhanced well-being to a greater extent than performance. Another meta-analytic review showed that time management was associated with a variety of beneficial employee outcomes, such as increased job satisfaction, job performance, and lower levels of stress and burnout [34]. Thus, managing time can directly improve one’s work-life balance. Time management training can enhance academics’ ability to prioritize tasks and manage workloads effectively [35].

When developing online interventions, pedagogical aspects are also important to consider. Reflective learning and experiential learning are 2 pedagogical approaches, which both emphasize the importance of personal experience and reflection in the learning process and in promoting deeper understanding [36,37]. Schön [36] introduced the concept of the “reflective practitioner,” highlighting the importance of reflection-in-action and reflection-on-action as mechanisms for professional growth and development, whereas Kolb’s [37] model underscores the interplay between experience and reflection, suggesting that effective learning requires individuals to engage in reflective observation to derive meaning from their experiences.

